## Methods

### Study Design

The SUN study is a parallel 3-arm, randomized controlled trial conducted in Auckland, New Zealand. A total of 300 infants who have not yet started CF are randomized using computer-generated randomization sequences in a 1:1:1 ratio to receive 1 of 2 daily prebiotic food interventions (double-blind standard kūmara powder or kūmara powder with banana powder containing RS) or be in the control arm (C) of the study.

### Participants and Recruitment

Infants are being recruited from the general population in urban central and greater areas of Auckland, New Zealand, from January 2022 to January 2024. Recruitment strategies include electronic and print advertising targeted toward postnatal and community groups, media releases, and appropriate social media platforms such as Facebook. All families that show interest in the study receive an email explaining the study in detail and are provided with the study participant information sheet and consent form.

### Ethical Considerations

The study was approved by the Health and Disability Ethics Committee of the Ministry of Health, New Zealand (reference 20/NTA/9). Parents or legal guardians are provided with an information sheet explaining the purpose of the trial; details of the research; specific procedures; benefits and risks; the voluntary nature of enrolment and the ability to opt out of the research at any time. A written informed consent form from the infant’s parents or legal guardian is an inclusion criterion, without which the infant cannot be included in the study.

Participants’ data are stored in a password-protected secure study database and are anonymized for analyses. The University of Auckland standards for data handling will be adhered to for data storage and management. No monetary compensation is provided for being in the trial, but on completion, parents are provided with a gift voucher as a thank you for taking part.

### Inclusion and Exclusion Criteria

Infants are eligible for participation in the study if they are healthy; are between 3 and 6 months of age; were at least 32 weeks gestation at birth; will be introduced to their first complimentary foods at around 6 months of age, and not before 4 months of age, as per the New Zealand Ministry of Health Food and Nutrition Guidelines for Infants [19]; and have parents or legal guardians that can provide written informed consent to participate in the study.

Infants are not eligible for participation if they were born <32 weeks gestation; were small for gestational age (as they may have special dietary requirements); have a developmental disability (ie, autism and intellectual disability); have an illness likely to influence their nutritional status (eg, a chronic illness known to cause malabsorption and any digestive or metabolic disorders); have health conditions that affect feeding; are undergoing treatment with antibiotics; have had any complementary foods at recruitment; are receiving a supplement with a prebiotic or probiotic; are not immunized according to the New Zealand Immunization Schedule; and have parents or legal guardians who have written or spoken English comprehension that is likely to make participation difficult for them.

Infants already taking a probiotic or prebiotic as a supplement are still eligible to participate if parents are willing to stop giving these to their infants.

### Randomization

The trial outline is shown in Figure 1. A “participant randomization form” was designed for the study on REDCap (Research Electronic Data Capture) tools hosted at the University of Auckland, which allows the independent administrator to randomly allocate the participant into the K, K+, or C group. Randomization is stratified by gender (female or male) using block randomization with variable block sizes of 3 or 6. The randomization list was prepared by the trial statistician (YJ) and is maintained by an independent database administrator. The lists are concealed until the point of randomization, and the 2 groups with kūmara intervention will remain double-blinded throughout the trial.

**Figure 1 figure1:**
[figure not shown]
Trial outline.

### Intervention

All participants randomized to either the K or K+ intervention groups are supplied with the kūmara powder at no cost to the participant. The kūmara powder is intended to be introduced alongside the first complementary food offered to participating infants and is to be consumed daily for a period of 4 months until the child is approximately 10 months of age. The kūmara powder is packaged in identical 5 g freeze-dried powder sachets and provided as a 2-month supply of study product at each of their clinic visits (baseline and midway through the study). A random number is assigned to each participant kit, using computer-generated sequences. For those randomized to receive one of the kūmara powders (K or K+), both study participants and the researchers will remain blinded throughout the trial.

Any kūmara powder not consumed within the 2-month interval is returned to the research team and recorded at the participant's next clinic visit. Adherence is measured using a daily consumption record completed by parents prospectively and information from a monthly questionnaire on the average amount of the kūmara powder consumed per day in the previous month. Participants randomized into the C group follow general feeding guidelines as per the New Zealand Ministry of Health [19] and receive gift vouchers at their clinic visits to the value of the kūmara powder as a token of appreciation for their continued participation.

### Compliance

Adherence to the kūmara powder is determined using a prospective daily record. Adherence will be defined as the consumption of 5 g of kūmara powder per day (approximately 1 tsp reconstituted with water) on 80% of the days within the monitored interval (ie, the previous month).

### Sample Size

A sample size of 80 participants per group will have 80% power at the 5% significance level (2-sided) to detect an absolute difference of 20% between the K+ and C groups on the primary outcome. This is equivalent to a 25% relative reduction, assuming a retention rate of 80%. To allow for a 20% loss to follow-up, we aim to recruit 300 participants in total (n=100 per group; Figure 1).

### Data Collection

Data collection takes place at baseline, when the child is 4-6 months of age, prior to commencing CF (CF1), and then around 8 months of age (CF2) and around 10 months of age (CF4) post randomization. Prior to the baseline clinic visit, written informed consent is obtained, and parents are given verbal and written information about participation. Questionnaires collecting information on sociodemographic characteristics and participating infant health are completed digitally using REDCap electronic data capture tools hosted by the University of Auckland [20]. At baseline, participants are assessed according to the schedule presented in Table 1 and either provided with a 2-month supply of kūmara powder or the equivalent value in gift vouchers (if randomized to the C group).

**Table 1 table1:** SUN^a^ trial schedule of enrolment, interventions, and assessments.

Timepoint			Study period											
			Enrollment		Allocation		Post allocation							Closeout
							Baseline		CF2		CF4			
Infant age			<4 mo		4-6 mo		≥4-6 mo		≤8 mo		≤10 mo		>10 mo	
**Enrollment**														
	Eligibility screen	✓												
	Informed consent	✓												
	Allocation			✓										
**Intervention**														
	Intervention A													
	Intervention B													
	Control													
**Assessments**														
	Measurements													
	Weight (kg)					✓		✓		✓				
	Length (cm)					✓		✓		✓				
	Questionnaires													
	Demographics	✓												
	Child health and nutrition	✓				✓		✓		✓				
	Maternal health and household	✓				✓				✓				
	Three×record-assisted 24-hour recalls							✓		✓				
	Daily health record					✓		✓		✓				
	Daily intervention adherence					✓		✓		✓				
	FFQ—maternal					✓		✓		✓				
	Sleep questionnaire—mother					✓		✓		✓				
	Biological sample collection													
	Infant													
	Feces					✓		✓		✓				
	Blood					✓				✓				
	5-Day sleep diary (using actigraphy)^b^					✓		✓		✓				
	Mother													
	Feces					✓		✓		✓				
	Breast milk					✓		✓		✓				
Completion and review of electronic trial documentation							✓		✓		✓			
Unblinding and data analyses													✓	

^a^SUN: seeding through feeding.

^b^An actigraph is a noninvasive method of recording infant sleep patterns through movement. The small sensor is fitted around the lower leg using a neoprene strap.

### Demographic Data

At baseline, information on family size (household structure, number of siblings, and presence of pets), parental education, parental occupation, parental ethnicity, living conditions, smoking habits, and family history of disease (eg, common allergens, including pets and pests, respiratory conditions, atopic disease, and chronic disease) is obtained. Information about the participating child includes birth weight and length, mode of delivery, initiation of breastfeeding, feeding patterns since birth, and health records, including hospital admissions and allergy history.

### Illness

Participating infants’ recent health history is captured prospectively via daily records of illness and use of medicines. The incidence and duration of illness or infections, including airway-related illness and gastrointestinal symptoms, are documented. Specific consent is obtained to contact the nominated family GPs to verify records of infection-related visits, medication prescription and use, and hospitalization events throughout the trial [16].

### Measuring Fecal Microbiota, Microbiome, SCFAs, and Rotavirus Vaccine–Specific Antibody Titer

Infant fecal samples are collected at 4-6 months of age (baseline), 8 (CF2), and 10 months of age (CF4) to assess the extent to which the kūmara interventions (K/K+ groups) and CF (all groups) have modulated the infant gut microbiota and to quantify rotavirus vaccine–specific antibody responses. Fecal samples are also analyzed for SCFAs by liquid chromatography-mass spectrometry using modifications to the method reported by Han et al [21]. to investigate the differences in fecal SCFAs and intermediate metabolites in infants in the different feeding interventions. Maternal fecal samples from consenting mothers are collected at baseline, CF2, and CF4 to assess the relationship between maternal and infant gut microbiota composition. The fecal microbial function is assessed using shotgun sequencing of metagenenomic DNA [22] using the Illumina HiSeq platform in conjunction with microbial profiling by pyrotag sequencing of 16S sRNA gene amplicons. Sequencing data will be analyzed using bioinformatics tools such as quantitative insights into microbial ecology [23], Rapid Annotation using Subsystems Technology for metagenomes [24], and Integrated Microbial Genomes [25]. The infant fecal metabolome is measured using high-resolution liquid chromatography–mass spectrometry using the method reported by Abshirini et al [26] to investigate differences in fecal metabolite profiles from the different feeding interventions over time.

### Measuring Rotavirus Vaccine–Specific Antibody Response and Immune Development in Blood

Venipuncture blood samples (this is an optional activity, so only infants whose caregivers will give specific consent) are collected by a trained pediatric phlebotomist at baseline (4-6 months of age) and CF4 (10 months of age). The total collected blood volume is approximately 5 mL (~0.7 mL/kg per 24 hours). Available blood samples will be used to assess the protective antibody response in plasma following oral rotavirus vaccination (administered at 6 weeks and 3 months of age), as well as the frequency of innate and adaptive immune cell subsets by spectral flow cytometry [27].

### Sleep

Quantitative infant sleep data are recorded using a standard ActiGraph (GT3X; Pensacola) worn at each timepoint continuously over 5 days. The actigraph is a watch-sized device fitted around the infant’s lower limb using a neoprene strap and is commonly used to measure sleep via sensing movement (acceleration), where the absence of movement infers sleep and movement infers wake [28,29]. The data will be processed for standard actigraphy sleep variables, inclusive of naps, using the count-scaled algorithm developed in MATLAB (MathWorks) [30]. Parents also record infant sleep in a sleep diary, which captures sleep-wake timing data across a 24-hour period for 5 consecutive days, and the Brief Infant Sleep Questionnaire, which is used to assess sleep patterns, parent perception, and sleep-related behaviors in young children (0-36 months) [31]. Validated parent-completed questionnaires on sleep-related impairment and sleep disturbance are used as a symptom assessment tool. These questionnaires measure 8 items on 5-point scales to rate the frequency of problems related to insufficient sleep and sleep disturbance in the past 7 days [32,33].

### Dietary Intake and Feeding Behaviors

Infant dietary intake is assessed using a 3-day food record at CF2 (infant approximately 8 months of age) and CF4 (infant approximately 10 months of age). Parents are asked to record the participating infant’s food and drink intake over 3 consecutive days, with even distribution across weekdays and weekends at a group level. Parents are instructed on how to complete the 3-day food records and use household measures to describe their infant’s dietary intake. Diet records will be analyzed with FoodWorks (version 10; Xyris Software) using the New Zealand Food Composition database FOODfiles 2018 (version 01).

At baseline (CF1), infant feeding practices such as method (breastfeeding, formula, or mixed feeding) and frequency or amount are recorded. A questionnaire at baseline and diet records at CF2 and CF4 captures the volume of milk intake (expressed breast milk or formula). Breast milk remains an important component of the diet and has important impacts on both the gut microbiota and immune function. Breast milk volume will be estimated using the previously validated methodology, whereby breastfeeding is recorded as time (minutes) and quantity estimated using a conversion factor of 10 mL/min, with a maximum of 10 minutes of breastfeeding or 100 mL of breast milk [34,35].

Habitual maternal food and nutrient intake will be assessed using a semiquantitative food frequency questionnaire, which has previously been validated in the New Zealand setting [36].

### Anthropometry

Anthropometric measurements are taken at baseline when the participating child is around 4-6 months of age (CF1), around 8 months of age (CF2), and around 10 months of age (CF4), using standardized protocols. Measurements include weight, length, and weight for length Z-scores [37].

### Measuring Breast Milk for Rotavirus Vaccine–Specific Antibody Titer and Secretory IgA

Breast milk samples are collected (where possible) from breastfeeding mothers at baseline, CF2, and CF4. Samples will be analyzed for rotavirus vaccine–specific titer quantification and the role of secretory IgA factors in shaping the gut microbiota during infancy and to examine the change in breast milk metabolome with prolonged breastfeeding (ie, beyond 6 months of age) and its continued modulating effect on infant gut microbiota diversity during CF. Sample collection is completed according to a predefined protocol, and breastfeeding mothers will have access to instructional videos on standardized sample collection (by hand expressing or pumping). To account for diurnal variation [38] and compositional differences between fore- and hindmilk [39], breast milk mothers are asked to express by emptying the full breast from the right side between 7 AM and 10 AM and at least 2-3 hours after a previous breastfeed. Wiping the breast with antiseptic (benzalkonium chloride) wipes to limit skin microbial contamination. After mixing the full sample by swirling or gently inverting, 15 mL of breast milk is decanted into a 15-mL falcon tube. Samples are kept in the fridge at home for up to 24 hours before the next clinic appointment. Samples are stored at –80 °C until analysis.

### Statistical Analysis

Participants’ data are stored in a secure study database and imported to SAS software (version 9.4; SAS Institute Inc) for data analysis at the end of the trial. The demographic and baseline characteristics of all randomized participants will be summarized for each group using descriptive statistics. Categorical variables will be described as frequencies and percentages. Continuous variables will be described as mean and SD or median and IQR as appropriate. Descriptive data on important subgroups (gender and ethnicity) will also be presented if a sufficient number of participants are recruited. No formal statistical tests will be conducted to compare the 3 groups at baseline, as recommended by the CONSORT guidelines [40].

There are 3 randomized groups (K+, K, and C) in the trial; however, the primary comparison will be based on the statistical test between K+ and C groups only. Additional comparisons between the other randomized groups will be conducted in secondary analysis using similar statistical models. This is to control the overall type 1 error rate, with the assumption that the proposed sample size will have sufficient power to detect the difference in primary outcome between the K+ and C groups. Primary outcome analysis will be conducted by intention-to-treat (where participants are analyzed according to their allocated treatment arm). The impact of missing data on the primary outcome will be explored in sensitivity analysis using different imputation strategies to test the robustness of the main results.

A secondary analysis of the primary outcomes will be conducted using a per-protocol population, including those participants in the intention-to-treat population who have no major protocol deviations. Inclusion in the per-protocol population and analysis will be based on the degree of intervention compliance, defined as the total number of days where less than the predefined amount of intervention food was consumed per day within the last study month. This information will be determined using a monthly intervention adherence record completed by parents or caregivers. Adherence will be defined as the consumption of 5 g of the intervention food per day on 80% of the days within the monitored interval.

Logistic regression models will be used to test the difference in the proportion of participants with at least 1 episode of RTI at a 4-month follow-up between the K+ and C groups (primary comparison), adjusted for gender (stratification factor). The effect of the intervention will be estimated between the 2 groups using a model-adjusted odds ratio with a 95% CI. Statistical tests will be 2-sided at a 5% significance level.

Generalized linear regression models will be used on other secondary outcomes to test the group differences at 2- and 4-month follow-ups separately, using a link function appropriate to the distribution of the outcome measure. All regression analyses will be adjusted for baseline outcome value (if available) and gender. The effect of the intervention will be estimated and tested using a model-adjusted point estimate on the group difference with a 95% CI and a 2-sided *P* value. Multiple testing on secondary outcomes will not be adjusted as they are considered exploratory and provide supporting information on the primary outcome. A random-effects mixed model will be used on the outcomes collected repeatedly over time to account for correlated data collected from the same participants and take into account any missing data in maximum likelihood estimates. The consistency of the short- and long-term effects of the dietary intervention will be assessed using the interaction term between the treatment group and visit. The effects of the intervention on predefined subgroups will also be assessed, and separate subgroup analyses will be considered if a sufficient number of participants are recruited.

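### The secondary per-protocol comparison of K+ with C selects on last-month powder adherence, which C cannot have and which an RTI may itself lower (should-fix)

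*Protocol article*

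**What the plan says.** All of this is in the protocol article. Under Statistical Analysis, intention-to-treat is primary, and "A secondary analysis of the primary outcomes will be conducted using a per-protocol population", made up of intention-to-treat participants without major protocol deviations. The next sentence ties membership to adherence: "Inclusion in the per-protocol population and analysis will be based on the degree of intervention compliance". Compliance is measured by the number of days on which "less than the predefined amount of intervention food was consumed per day within the last study month". The threshold follows: "Adherence will be defined as the consumption of 5 g of the intervention food per day on 80% of the days within the monitored interval".

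Under Intervention, "All participants randomized to either the K or K+ intervention groups are supplied with the kūmara powder", whereas "Participants randomized into the C group follow general feeding guidelines as per the New Zealand Ministry of Health" and receive vouchers. No adherence criterion is given for C.

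The primary model, also under Statistical Analysis, compares K+ with C on the proportion of infants with at least one RTI episode at the 4-month follow-up.

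**The concern.** The rule has three weaknesses for K+ versus C.

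- **It applies to one side only.** C infants eat no intervention food. Applied as written, the rule empties C and leaves nothing to compare. Applied in the only workable way, it removes infants from K+ and none from C, so the comparison is no longer between randomized groups.
- **The selection window lies inside the outcome window.** Adherence is judged in the last month, and RTIs in that month count toward the endpoint. If a sick infant takes less powder, an RTI can remove its own case, and only from K+.
- **Months 1 to 3 are ignored.** An infant who took little powder for three months can qualify on the last month alone, although RTIs in all four months count.

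At stake is a prespecified analysis of the primary outcome. It could show a benefit for K+ that intention-to-treat does not, with no adjustment for the selection described.

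**Working it through.** **1. The plan's own figure.** Under Sample Size, a 20-point absolute difference equal to a 25% relative reduction implies 0.20/0.25 = 80% RTI in C and 60% in K+. At two-sided 5% and 80% power, the unpooled formula gives (1.960 + 0.842)² × (0.8×0.2 + 0.6×0.4)/0.2² = 78.5, so 79 per group; the pooled formula gives 82. Power at 80 per group is 79.4% (pooled) to 80.7% (unpooled). With 20% loss, 80/0.8 = 100 per group. The stated figures reproduce, so 80% base risk and 80 per arm are used below.

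**2. How tight the rule is.** In a 30-day month, 80% is 24 days. At most 6 days may be missed or partial, so about a week of reduced intake excludes an infant.

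**3. Model under no true effect.**
- R = 0.80, the 4-month RTI risk in both arms (from step 1).
- q = probability of an RTI in the last month. With a constant monthly risk (assumption), q = 1 − (1 − 0.80)^(1/4) = 0.331.
- a0 = 0.80, the probability of meeting the rule without a last-month RTI (assumption).
- a1 = the same probability with a last-month RTI (assumption, varied).
- C is unfiltered at n = 80; K+ is 80 before exclusion.

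Proportion of K+ kept: D = q·a1 + (1 − q)·a0.

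Per-protocol RTI risk in K+: [q·a1 + (R − q)·a0] / D.

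Example, a1 = 0.40: numerator 0.331×0.40 + 0.469×0.80 = 0.507; D = 0.331×0.40 + 0.669×0.80 = 0.667; risk = 0.760.

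Rejection is from the two-sided 5% pooled z-test of 80 controls against 80·D infants in K+.

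| a1 | K+ kept | K+ risk | Spurious difference | Odds ratio | Two-sided rejection |
|---|---|---|---|---|---|
| 0.80 (no link) | 64 | 80.0% | 0 | 1.00 | 5.0% |
| 0.70 | 61 | 79.1% | 0.9 points | 0.95 | 5.2% |
| 0.60 | 59 | 78.2% | 1.8 points | 0.90 | 5.9% |
| 0.50 | 56 | 77.2% | 2.8 points | 0.84 | 7.0% |
| 0.40 | 53 | 76.0% | 4.0 points | 0.79 | 8.8% |
| 0 (every last-month RTI excluded) | 43 | 70.1% | 9.9 points | 0.59 | 24.3% |

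Simulation agrees to within about 0.2 percentage points. With a1 = 0.40, 8.1% of trials show a significant K+ benefit, against 2.5% with no link.

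**4. Sensitivity.** Taking a0 as 0.70 or 0.90 and halving adherence after a last-month RTI leaves the K+ risk at 76.0%, with rejection 8.6% to 8.9%. Varying q from 0.20 to 0.60, again with adherence halved, moves the odds ratio from 0.88 to 0.62. The constant-monthly-risk assumption therefore matters.

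**The case against.** **The analysis is secondary.** This stands. The primary K+ versus C test, the sample size and the type 1 error statement all rest on intention-to-treat and are untouched.

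**The illness–adherence link is not in the documents.** This stands. No adherence rates are given, and the daily amount is about a teaspoon. Another pattern is possible: attentive parents might both adhere better and visit the GP more, which would bias against K+. The direction toward K+ depends on the assumed link.

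**How C enters the set could be settled in the SAP.** This stands only in part. The clause on major protocol deviations might remove some C infants. But the article does not simply leave the matter open; it bases inclusion on intake of a product that C never receives, and that rule works badly as written.

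**A stronger reading.** A reader might infer a much larger artefact by letting an RTI at any time in the 4 months lower last-month adherence. With a1 = 0.40 for every RTI case, the K+ risk is 0.8×0.4/(0.8×0.4 + 0.2×0.8) = 66.7%, a spurious 13 points with about 36% rejection. The mechanism that the text makes plausible is an RTI in the last month. Under a constant monthly risk only 0.331/0.80 = 41% of RTI cases have one, and the other 59% would adhere at 0.80. Average adherence among RTI cases then cannot fall below 0.59 × 0.80 = 0.47, so a value of 0.40 is out of reach. The larger figures need a wider link, or more RTIs in the last month, and the documents support neither.

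**Conclusion.** The point holds as a should-fix. From the text alone, the per-protocol rule either excludes all of C or filters only K+ in the primary pairing, on post-randomization behaviour inside the outcome window and without regard to months 1 to 3.

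The size rests on assumptions: that an RTI lowers intake, a constant monthly risk, and 80% adherence otherwise. On these, the artefact is about 1 to 4 points with 5% to 9% rejection. The extreme, in which every last-month RTI excludes the infant, is about 10 points and 24%; that is half of the 20-point design effect. With no link, this mechanism gives no bias.

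The documents do not support saying that the trial's main conclusion is at risk, or that the per-protocol result will certainly favour K+.

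**What to change.** 1. **K+ versus C.** Replace the naive per-protocol comparison with a complier-average causal effect that keeps all randomized infants. Use one binary adherence definition: the plan's 5 g on at least 80% of all days from randomization to CF4, taken from the daily record. Estimate the effect as the intention-to-treat risk difference divided by the proportion adherent in K+, with a bootstrap confidence interval. With no true effect this targets zero whether or not illness lowers adherence.
2. **State the exclusion restriction.** Allocation is assumed to act only through adherent intake. The unblinded control arm and intake below the threshold may both strain this. The divisor must match the definition: the adherent proportion belongs to binary adherence, not to a proportion-of-days measure.
3. **K+ versus K.** Keep the adherence-based per-protocol set only here, with the same whole-period window, since one rule then applies to both blinded arms.
4. **Any remaining K+ versus C per-protocol result.** Label it descriptive and say how C enters the set.

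The cost is a change of wording and one extra analysis on data already collected. Confidence intervals will be wider. For example, if 70% of K+ adhered (assumption), the standard error at 80% risk and 80 per arm would be √(2×0.16/80)/0.70 = 0.090, against √(0.16/80 + 0.16/56) = 0.070 for the naive comparison.

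### Per-protocol inclusion rests on an inconsistently named adherence source and on the last of four intervention months only; the daily record already planned can supply both source and full window

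*Protocol article*

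**What the plan says.** Four places in the protocol article bear on this.

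- **Statistical Analysis, per-protocol paragraph.** Inclusion depends on how well the product was taken, a quantity "defined as the total number of days where less than the predefined amount of intervention food was consumed per day within the last study month". On the source it says: "This information will be determined using a monthly intervention adherence record completed by parents or caregivers". The threshold follows: "Adherence will be defined as the consumption of 5 g of the intervention food per day on 80% of the days within the monitored interval".
- **Compliance.** "Adherence to the kūmara powder is determined using a prospective daily record". The same 5 g on 80% of days applies, and the monitored interval is given as the previous month.
- **Intervention.** Two instruments are described. One is a daily form ("Adherence is measured using a daily consumption record completed by parents prospectively"). The other is "information from a monthly questionnaire on the average amount of the kūmara powder consumed per day in the previous month". Unused powder is also returned and recorded at the next clinic visit.
- **Table 1 (Data Collection).** Daily intervention adherence is scheduled. No separate monthly adherence item appears.

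The powder is taken daily for four months. The primary analysis compares the proportions of infants with one or more RTI episodes at the four-month follow-up.

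**The concern.** There are two separate weaknesses.

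**Source.** The rule needs a count of days. The Compliance section takes it from a daily record; the Statistical Analysis section takes it from a monthly record that is described nowhere else under that name. The only monthly adherence instrument that is described yields an average, and an average does not determine a day count. While this is open, an analyst could choose between two sources that may classify the same infant differently.

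**Window.** Per-protocol status is judged on one month, while exposure runs for four and the outcome is read at the end of the four. An infant can be labelled adherent, or not, on a month that says little about exposure when an early infection occurred. The per-protocol estimate is meant to describe infants who took the product as intended, and a last-month rule does not select that group.

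**Working it through.** The protocol gives no computed figure for this rule, so there is none to reproduce. The sample size does not depend on it.

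**Inputs.** 5 g per day, 80% of days, one-month interval (Compliance; Statistical Analysis); 5 g sachets and four months of daily use (Intervention). Assumptions: a 30-day month, at most 5 g per day, and four such months = 120 days.

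**Step 1: the rule from daily data.** Full days needed = 0.80 × 30 = 24, so at most 30 − 24 = 6 short days. For other month lengths, rounding up: 23 of 28, or 25 of 31. A daily record gives this count directly.

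**Step 2: the rule from a monthly average.** For an average of *a* g/day, the most full days possible is 30*a*/5 = 6*a*, rounded down. For any *a* below 5 the fewest is 0, because every day could have been at *a*.

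| Average (g/day) | Fewest full days | Most full days | Meets 80%? |
|---|---|---|---|
| 3.5 | 0 | 21 (70%) | No |
| 4.0 | 0 | 24 (80%) | Undetermined |
| 4.5 | 0 | 27 (90%) | Undetermined |
| 4.9 | 0 | 29 (97%) | Undetermined |
| 5.0 | 30 | 30 (100%) | Yes |

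At 4.0 g, for example, 24 × 5 / 30 = 4.0 (adherent) and 30 × 4 / 30 = 4.0 (no full day). Status is settled only below 4.0 g or at exactly 5 g. The lower edge of the undetermined band is 23 × 5 / 28 = 4.11 g in a 28-day month and 25 × 5 / 31 = 4.03 g in a 31-day month. Without the 5 g daily cap, an average of 5 g or more would not settle status either.

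**Step 3: last month against all four.** The whole-period threshold is 0.80 × 120 = 96 full days.

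| Full days, months 1–3 (of 90) | Full days, month 4 (of 30) | Last-month rule | Four-month percentage |
|---|---|---|---|
| 0 | 24 | Met (80%) | 24/120 = 20%: not met |
| 90 | 6 | Not met (20%) | 96/120 = 80%: met |
| 90 | 23 | Not met (77%) | 113/120 = 94%: met |
| 90 | 0 | Not met (0%) | 90/120 = 75%: not met |

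The two windows can disagree in both directions. They agree on the infant who takes every dose for three months and then stops completely.

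**The case against.** A reader might infer that the 80%-of-days rule cannot be applied at all, or that the per-protocol set will be recall-based and misclassified. The documents do not support that. A prospective daily record is described in the Intervention and Compliance sections and scheduled in Table 1, and it supplies the count. Nor does any section equate the monthly record in the Statistical Analysis section with the average-amount questionnaire. One is called a record and the other a questionnaire, and the first is said to yield a number of days. It could be a monthly sheet of daily entries, which would fit the one-month interval in the Compliance section. That reading is reasonable, but the article does not state it, so the ambiguity stands and the arithmetic on averages matters only if the questionnaire is used.

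On the window, two replies deserve weight. Both sections use a one-month interval, so this is a weakness of the rule and not a contradiction between sections. Also, per-protocol infants must be free of major deviations, and a condensed article may leave that list to the full protocol or SAP. Such a list might remove an infant with no intake for three months. But the next sentence of the article bases inclusion on last-month compliance, so the clause does not clearly prevent the problem.

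Finally, this is a secondary analysis, and which form feeds a flag is often left to the SAP. That argues for minor severity. It does not remove the point, because the article itself names a source and a window.

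**Conclusion.** The point holds in limited form. The adherence source for per-protocol membership is named inconsistently, and the last-month window does not match a four-month intervention with an outcome read at four months. If the average-amount questionnaire were used, status would be undetermined for averages from 4.0 g to just under 5 g per day (30-day month, 5 g daily cap). As the window is written, an infant with 20% of full days overall can meet the compliance criterion and one with 94% can fail it. The window point assumes that RTI episodes count over the whole four months, as the wording of the primary analysis suggests.

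The documents give no figures on part-sachet use or on how adherence varies by month, so the number of infants affected is unknown. The effect is confined to the secondary per-protocol analysis. The intention-to-treat primary comparison, its type 1 error and the sample size are untouched. Severity: minor.

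**What to change.** In the per-protocol paragraph of Statistical Analysis, replace the monthly source and the last-month window. State that membership is derived from the prospective daily consumption record, as the percentage of days meeting the predefined amount over the whole four-month intervention period, keeping the protocol's own 80% threshold. Use returned powder as a check on total consumption. Reserve the monthly questionnaire for a sensitivity analysis where daily records are missing.

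The interval in the Compliance section then needs reconciling: either give it the same four-month window, or say that the previous-month interval serves ongoing monitoring and not per-protocol membership.

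The cost is small edits in two sections and no new data, since the daily record, the returns and the questionnaire are already collected. The downside is that infants with incomplete daily records may leave the per-protocol set. The handling of missing days should therefore be fixed before unblinding.
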